**Fig. 2 Fig2:**
[figure not shown]
Study flow diagram

### Setting

The study will be conducted at multiple EDs in SingHealth, the largest public healthcare group in Singapore. Recruitment sites will include Singapore General Hospital (SGH), Changi General Hospital (CGH), and Sengkang General Hospital (SKH). All patients will be triaged based on severity using the Singapore Patient Acuity Category Scale [40]. Chest pain is the presenting complaint in up to 40% of triage level 1 and 2 cases (the most severe triage categories) [41].

### Participants & procedures

Participants will be recruited and assessed for eligibility by clinical research coordinators stationed in the ED during peak operating hours. To reduce the potential for attrition, participants will be given the option of completing follow-up assessments in person or by telephone.

Eligible participants at the first stage will be English- or Chinese-speaking men and women aged 21–70 years, who are assigned to triage level 2 (possibly critical) or 3 (minor emergency). They will need to present with at least one primary complaint consistent with a possible panic attack (e.g., tachycardia, chest pain, shortness of breath, dizziness, hyperventilation). Patients who are initially assigned to triage level 1 (critical illness requiring resuscitation) and subsequently downgraded to a non-life-threatening condition will also be eligible. We will exclude patients who are assigned to triage level 1 and deemed to have a life-threatening condition, who present with altered mental status (e.g., dementia, psychosis, substance intoxication or withdrawal) that would impact their ability to provide informed consent, who have symptoms with a clear cardiac or other medical cause (as confirmed by laboratory results and the ED physician), and who are unable or unwilling to complete the study procedures (See Table 1).

**Table 1 Tab1:** Inclusion and exclusion criteria at each stage of the study

Stage 1: Screening	
*Inclusion Criteria:* 1. Male or female 2. 21+ years of age 3. Triage level 1 (not life-threatening condition), 2, or 3 4. English or Mandarin speaking 5. Able to provide informed consent and read study materials 6. Presenting complaint of chest pain, palpitations, dizziness, or breathing difficulties 7. Score ≥ 3 on the CDR screener	*Exclusion Criteria:* 1. Altered mental status (dementia, psychosis, substance intoxication/withdrawal) 2. Prisoner or police case 3. History of psychosis or schizophrenia or actively suicidal 4. Life-threatening condition requiring resuscitation 5. Not English- or Mandarin-speaking 6. Unwilling or unable to complete study procedures 7. Clear organic cause for panic symptoms as symptoms of potentially life threatening organic disease (e.g., acute coronary syndrome, STEMI, NSTEMI, angina pectoris), pneumothorax, aortic dissection, pulmonary embolism, tumour, effusion, rib fractures, pneumonia as determined by the ED physician
Stage 2: Randomization	
*Inclusion Criteria:* 1. Diagnosis of panic attack or panic disorder confirmed by the SCID interview 2. Willing to enter randomized trial	*Exclusion Criteria:* 1. Does not meet criteria for panic attack or panic disorder based on the SCID interview 2. Received CBT for panic symptoms in the last 12 months 3. Unwilling to enter randomized trial

In order to maximize generalizability to the broad group of patients with panic symptoms who present to the ED, we will not exclude patients who have received other types of psychotherapy for panic symptoms or those who are being treated with antidepressant medications. However, we will assess for these treatments at each time point and we will control for ancillary treatments in subsequent analyses. Patients who have received CBT for panic symptoms in the prior 12 months will be excluded.

### Interventions

Participants in both the SCREEN and STEP arms will follow the typical care pathway in the ED, which includes medical evaluation of their presenting complaint, any investigations ordered by the ED physician, reassurance that their symptoms are not indicative of acute coronary syndrome or other life-threatening illnesses, and outpatient follow-up as recommended at discharge. Participants in the SCREEN arm will be given the results of the screening interview, but no other protocol interventions. Participants in the STEP arm will be given a 1-hour psychoeducation session consisting of information regarding the nature and causes of panic attacks and behavioural strategies to manage future attacks. They will also be provided with written materials for future reference. Patients in the STEP arm who do not improve with psychoeducation will receive CBT based on a brief manualized protocol consisting of five weekly 1-hour individual sessions; the sessions will focus on cognitive restructuring and exposure to panic symptoms [42]. The psychoeducation and CBT sessions will be delivered by a trained clinical psychologist in either English or Mandarin, depending on the patient’s preference.

### Outcome measures

Outcome measures were selected to 1) provide adequate coverage of the core symptoms of panic attacks, panic disorder, and comorbid psychiatric conditions (e.g., depression, generalized anxiety disorder, substance use disorders), 2) assess disability and quality of life as well as symptom severity, and 3) have acceptable psychometric properties in English and Chinese. Whenever possible, we chose outcome measures that have been widely used in other clinical trials on panic disorder to facilitate comparison with other studies (i.e., in subsequent meta-analyses). In addition to clinician-rated and patient-reported outcome measures, we will collect service-use data from patient medical and billing records, and will ask patients to report on their use of ancillary treatments (e.g., other types of counselling, traditional Chinese medicine, stress management programs) and psychotropic medications at each assessment visit.

Clinician-rated outcomes: We will use the following clinician-rated assessment instruments to assess the outcomes under Aim 1.

*Clinical Decision Rule (CDR)*: The study team has developed a brief 7-item screening tool that can quickly distinguish between ED patients with or without panic-related anxiety [8]. The CDR consists of the following symptoms: 1) palpitations, pounding heart, or accelerated heart rate, 2) derealization, 3) paresthesia, 4) sensations of shortness of breath or smothering, 5) chills or hot flushes, 6) feeling dizzy, unsteady, lightheaded, or faint, and 7) fear of losing control or going crazy. The CDR is scored by assigning 1 point for each positive symptom. It has demonstrated excellent overall separation between patients with or without panic-related anxiety (area under the receiver operating characteristic curve = 0.90). At a cut- off score of 3 or greater, the CDR has a good balance between sensitivity (81.7%) and specificity (87.9%) [8].

*Panic Disorder Module of the Structured Clinical Interview for DSM-5 (SCID)*: The SCID is the gold standard tool for the reliable diagnosis of Axis I psychiatric disorders in clinical populations [32]. The study team has extensive experience using the panic disorder module of the SCID in previous ED studies [8, 43]. We found that inter-rater reliability was excellent for panic attacks (κ = 1.00) and panic disorder (κ = 0.82), indicating that the interviewers were able to assess panic symptoms with a high degree of accuracy.

*Panic Disorder Severity Scale (PDSS)*: The PDSS is a 7-item semi-structured interview to evaluate panic symptom severity [30]. It contains items that assess the frequency of panic attacks, level of distress during panic attacks, anticipatory anxiety, agoraphobic fear and avoidance, interoceptive fear and avoidance, impairment of occupational functioning, and impairment of social functioning. Each item is rated on a 0 (none/mild) to 4 (extreme/severe) scale. The English and Chinese versions of the PDSS have demonstrated good convergent/discriminant validity, internal consistency, inter-rater reliability, and test-retest reliability [30, 44–46]. PDSS scores are sensitive to treatment response and are recommended for treatment monitoring [12].

*Clinician Global Impression (CGI) severity scale*: The CGI is a clinician-rated instrument used to assess global severity of symptoms [31]. The CGI ranges from 1 (normal, not at all ill) to 7 (among the most extremely ill patients). The Singapore Clinical Practice Guidelines for Anxiety Disorders recommend using the CGI to measure illness severity and treatment progress during consultations for anxiety disorders [12]. Specific anchor points are used to delineate the domains of information to be assessed in scoring the CGI for patients with panic disorder [47]. The following parameters are assessed: number and frequency of panic attacks, intensity of anticipatory anxiety, degree of phobic avoidance, and functional impairment. The panic CGI has been successfully used in clinical trials for panic disorder and has established an inter-rater reliability of 0.89 [47].

Patient-reported outcomes: We will use the following instruments to assess the patient-centred outcomes under Aims 2 and 3. All patient-reported outcomes have strong psychometric properties, are available in English and Chinese, and have been used in local studies conducted by the study team.

*Short Form Health Survey (SF-12)*: The SF-12 is a reliable and valid 12-item self-report questionnaire that evaluates eight facets of health-related quality of life [33, 48]. It includes subscales to assess physical functioning, role limitations due to physical health problems, role limitations due to emotional problems, bodily pain, general health, vitality, social functioning, and mental health. The SF-12 will be used to assess health-related quality of life by converting the results into a quality of life weight using the SF-6D algorithm [36].

*Psychiatric Diagnostic Screening Questionnaire (PDSQ)*: The PDSQ is a reliable and valid self-report diagnostic questionnaire that has been widely used to assess the most common psychiatric disorders in outpatient settings, including major depressive disorder, generalized anxiety disorder, panic disorder, posttraumatic stress disorder, alcohol abuse/dependence, drug abuse/dependence, psychosis, bulimia/binge eating disorder, and somatization disorder [35]. It includes 125 yes/no items that can be summed for a total score, which functions as a global indicator of psychopathology.

*EuroQoL- 5 Dimension (EQ-5D)*: The EQ-5D is a patient self-report instrument that evaluates health-related quality of life [34] . It includes one question each to assess mobility, self-care, usual activities, pain/discomfort, and anxiety/depression, as well as a Visual Analog Scale (VAS) that asks respondents to rate their perceived health status from 0 (the worst possible health status) to 100 (the best possible health status).

### Criteria for ‘stepping up’ in the stepped-care intervention arm

The decision to step-up interventions for patients in the STEP arm will be guided by remission status as assessed by the PDSS and CGI. Acute remission status is defined by a CGI score of 1 or 2 (no disorder or borderline disorder) and no panic attacks for a one-week period. Full remission is defined by maintenance of this status for two consecutive months [49]. Participants who show acute remission of panic symptoms one month after completing the psychoeducation session will enter the follow-up phase. Those who do not show acute remission of panic symptoms at one-month post-psychoeducation or return to the ED with panic symptoms within three months will be stepped up to receive the 5-session CBT protocol.

### Treatment fidelity

All CBT sessions in the STEP arm will be recorded with patient permission. A subset of 20% of the recordings will be reviewed and scored by for adherence to the study protocol using the CBT subscale of the Collaborative Study Psychotherapy Rating Scale (CSPRS), a psychometrically-sound tool for assessing adherence to CBT intervention in clinical trials [50].

### Participant timeline

Participants in both arms will be involved in the trial for a period of 12 months. Following recruitment at baseline at the ED, masked follow-up assessments will be conducted by an independent interviewer at 1, 3, 6, and 12 months. The timeline of study assessments is shown in Table 2. Participants in the STEP arm will receive psychoeducation within 1 week of discharge from the ED and those who are stepped-up will receive 5 weekly sessions of CBT between the 1-month and 3-month follow-up.

**Table 2 Tab2:** Timeline of study assessments

Construct	Outcome Measure	Time point					
		Screening	Baseline	1 month	3 months	6 months	12 months
Panic Screening	CDR^a^	x					
Panic Attack/Disorder Diagnosis	SCID Panic Module^a^		x	x	x	x	x
Panic Symptom Severity	PDSS^a^		x	x	x	x	x
	CGI^a^		x	x	x	x	x
Psychiatric Comorbidity	PDSQ^b^		x	x	x	x	x
Health-Related Quality of Life	SF-12^b^		x	x	x	x	x
Healthcare Utilization	Electronic medical record						x
Direct Healthcare Costs	Electronic billing data						x
Cost Effectiveness	SF-6D/EQ-5D^b^		x	x	x	x	x

^a^Clinician-rated outcomes. ^b^Patient-reported outcomes

*CDR* Clinical Decision Rule; *SCID5 RV* Structured Clinical Interview for DSM-5; *PDSS* Panic Disorder Severity Scale; *CGI* Clinical Global Impressions Severity Scale; *PDSQ* Psychiatric Diagnostic Screening Questionnaire; *SF-12* Short Form Health Survey; *EQ-5D* EuroQoL- 5 Dimension

### Sample size

We will aim to recruit a randomized sample of 212 participants. Sample size was estimated based on change in panic symptom severity with PDSS score at 1-month post-intervention as the primary outcome. Previous studies of the 5-session CBT protocol for patients with panic disorder showed relatively large effect size changes on the PDSS from pre- to post-intervention [42] (Cohen’s d = 2.03–2.62). Based on previous literature, we expect a more modest effect size change for the psychoeducation intervention alone [24]. Assuming the true difference between treatments to be 0.516 times the common standard deviation (i.e., Cohen’s d = 0.516, which is approximately Cohen’s medium effect size), a final sample size of 80 participants in each group (after accounting for 25% attrition) would ensure 90% power at a two-sided 0.05 significance level.

### Randomization

Patients will be randomly allocated to one of the two arms based on a code generated using the open-source software R (https://www.r-project.org) and contained within sequential sealed envelopes. We will stratify the participants by the diagnosis of panic attack or panic disorder. Within each stratum, we will apply a permuted block randomization scheme with a block size of 4 and a 1:1 randomization ratio between the screening alone (SCREEN) or stepped-care intervention (STEP) arms. This permuted block randomization will ensure balance in the trial. The randomization block will be generated before commencing the study at the various sites. The study coordinator will proceed to open the randomisation envelopes to reveal the allocation only after a patient has been enrolled in the trial.

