## Study status

This trial commenced in June 2018. Baseline recruitment is still ongoing, with a planned end date of February 2023. Follow-up data collection will continue until February 2024.

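### With one published block size of 4 in each diagnosis stratum, up to a third of allocations could be deduced in advance by a recruiter who sees the whole list

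*Protocol article*

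**What the plan says.** The Randomization section of the protocol article sets these features:

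- Strata: "We will stratify the participants by the diagnosis of panic attack or panic disorder". Site is not named as a stratum.
- Blocks: "we will apply a permuted block randomization scheme with a block size of 4", with "a 1:1 randomization ratio between the screening alone (SCREEN) or stepped-care intervention (STEP) arms".
- Concealment: the codes are "contained within sequential sealed envelopes".
- Opening: "The study coordinator will proceed to open the randomisation envelopes to reveal the allocation", and this happens only once the patient is in the trial.

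The stratum is known before allocation, because a Stage 2 entry criterion in Table 1 is "Diagnosis of panic attack or panic disorder confirmed by the SCID interview". Under Participants & procedures, "Participants will be recruited and assessed for eligibility by clinical research coordinators stationed in the ED during peak operating hours". Under Masked follow-ups, site coordinators carry out the masking, the follow-up assessor is blind to allocation, and participants cannot be. The Setting section names three hospitals. Study status says "Baseline recruitment is still ongoing, with a planned end date of February 2023", so the block size became public while patients were still being entered.

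**The concern.** Sealed envelopes stop anyone from reading the next allocation. They do not stop anyone from working it out. When the block size is constant and known, a person who has seen the earlier allocations in a list can count how many places each arm has left in the current block. Once one arm is used up, the rest of the block is certain.

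This matters at entry. Stage 2 requires that the patient be willing to be randomized, and how and when a patient is approached leaves some discretion. The arms differ visibly: psychoeducation with possible CBT in one, the screening result alone in the other. A recruiter who expects a particular arm could, knowingly or not, press harder or hold back. The groups would then differ at baseline for reasons other than chance, and an analysis can adjust only for the differences that were measured.

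**Working it through.** **The plan's own figures.** The article gives no predictability figure. Its sample size, from which the 212 used below comes, reproduces. With d = 0.516, two-sided alpha 0.05 and 90% power, the normal approximation gives 79 per group; 79/0.75 = 105.3, so 106 per arm and 212 in total. Starting from 80 per group gives 80/0.75 = 106.7, so 107 per arm and 214, a negligible difference. Nothing below changes the sample size.

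**Inputs.** Block size 4, ratio 1:1, strata by diagnosis, 212 randomized, three sites (Randomization, Sample size, Setting).

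**Certain allocations, observer sees the whole list.** A 1:1 block of 4 has 6 equally likely orders.

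- Positions 1 and 2: never certain.
- Position 3: certain when the first two match, which is 2 of 6 orders = 1/3.
- Position 4: always certain.

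Share = (0 + 0 + 1/3 + 1)/4 = 33.3%. Applied to 212: 212/3 = 70.7, about 71 patients.

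**Best-guess accuracy, same observer.** The guess is the arm with more places left, or a coin toss if they are equal.

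- Position 1: 1/2.
- Position 2: 2/3.
- Position 3: (1/3)(1) + (2/3)(1/2) = 2/3.
- Position 4: 1.

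Mean = (1/2 + 2/3 + 2/3 + 1)/4 = 70.8%, against 50% under simple randomization.

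**Certain allocations, one list per stratum shared by three sites.** Assumptions: patients come equally from three sites, each coordinator sees only allocations at their own site, and the position in the block is known.

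- Position 3 is certain only if both earlier patients were at the same site as the third, (1/3)² = 1/9, and were given the same arm, 1/3. Probability 1/27.
- Position 4 is certain only if the two matching patients among the first three were both at that site. Probability 1/9 = 3/27.

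Share = (1/27 + 3/27)/4 = 1/27 = 3.7%.

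**Alternatives, observer sees the whole list.** A fixed block of 2m gives a certain share of 1/(m + 1). For randomly mixed sizes the figures are simulated, for an observer who knows the set of possible sizes and every past allocation and updates accordingly (106 patients per list, an assumption; lists of 36 give much the same result).

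| Scheme | Certain | Best guess correct | Maximum imbalance per list |
|---|---|---|---|
| Fixed 4 (plan) | 33% | 71% | 2 |
| Fixed 6 | 25% | 68% | 3 |
| Fixed 8 | 20% | 67% | 4 |
| Random 4, 6 | about 5% | 69% | 3 |
| Random 4, 6, 8 | 2–3% | 68% | 4 |

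Mixing sizes removes most of the certainty. It hardly changes guessing.

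**The case against.** Several objections carry weight.

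- **List structure is not stated.** The article does not say whether each site holds its own envelopes or all three draw on one list per stratum. Site-held sets give the full third; a shared list with no exchange of information gives about 4%. The article condenses a fuller protocol (version 4.0) that is not shown, so its silence on this is not itself a fault. The fixed block size, however, is stated and not merely left out. This objection limits the size of the point and does not remove it.
- **Staff identity is inferred.** The article speaks of clinical research coordinators, the study coordinator and site coordinators. That these are the same people is the natural reading, but it is not written, and nowhere is it said that each of them sees every past allocation.
- **Room for steering is limited.** Entry needs a score of at least 3 on the screening rule and a SCID-confirmed diagnosis, and the ED physician decides whether there is an organic cause. The discretion that remains lies mainly in approach and consent.
- **Outcome raters are masked.** A reader might infer that predictable allocation combines with unmasked rating. The article does not support that: follow-up assessors are independent and blind. Their masking protects the ratings but not selection at entry.
- **Some adjustment is possible.** PDSS and CGI are measured at baseline, before randomization, so selection on measured severity would be visible and could be adjusted for. Selection on unmeasured factors could not be fully corrected.

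**Conclusion.** The point holds as a cheap improvement to concealment, with a stated range. Up to one-third of allocations, about 71 of 212, could be deduced with certainty by a recruiter who knows the block size and sees all earlier allocations in a list, as would be so with site-held envelope sets. If one list per stratum is shared by three equal sites without shared information, the figure is about 4%.

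A reader might go further and conclude that a third of allocations are in fact known in advance, or that the trial is biased. The article supports neither. The first needs a list structure and a division of duties that it does not give. The second needs evidence of steering, and there is none either way. The arithmetic for the block is exact; its application to this trial rests on the assumptions named.

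**What to change.** While recruitment is open, have someone outside recruitment regenerate the R list for all unused envelopes, with randomly varying block sizes (4, 6 and 8, for example) within each existing list. Withhold the sizes from the coordinators and do not publish them before recruitment ends. Allocations already made stand. Record in the protocol whether lists are held by site or shared, since this decides where in the 4% to 33% range the present scheme lies.

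The gain, for an observer who sees the whole list, is a fall in certain allocations from 33% to about 5% (sizes 4 and 6) or 2–3% (sizes 4, 6 and 8). Best-guess accuracy falls only from 71% to about 68–69%, so the change removes certainty rather than predictability. It also leaves recruiting and envelope opening with the same staff, if that is the present arrangement.

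The cost is one new list, one re-issue of envelopes and a protocol note. Maximum imbalance per list rises from 2 to 4, or to 3 with sizes 4 and 6. With six lists (three sites, two strata), the summed worst case goes from 6 × 2 = 12 to 6 × 4 = 24 among 212, which is very unlikely to be reached. The sample size does not change.

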### Masked follow-ups

Masking will be carried out by the individual study site coordinators. The follow up assessments will be conducted by a masked team member who is blind to allocation. However, as this is a psychotherapy trial, it will not be possible to blind participants with respect to their own allocation.

